### Trial Intervention/Treatments

This study will be a prospective, cohort study. The study will evaluate two interventions: real-time audio-visual feedback during CPR and real-time audio-visual feedback during CPR plus post event feedback using the Q-CPR system (described below). We have not included a 3rd arm (post event feedback alone) as this would be unlikely to be used in clinical practice as to be able to provide this model of post event feedback requires the use of the Q-CPR equipment, which incorporates the real-time audiovisual feedback facility.

The study will be divided into 2 phases (see table 1). During the first phase, baseline data will be collected at each site without any intervention. During the second phase, real-time feedback phase will be implemented at one site (Good Hope-GH) and real-time audiovisual feedback plus post event debriefing at one site (Heartlands-BHH). The remaining site (Solihull-SH) will act as the control site during both interventions. The purpose of the control site is to exclude any Trust-wide or other temporal changes in care as potential explanations for any changes in outcomes at Heartlands/Good Hope.

**Table 1 T1:** Showing the two phases and interventions at the 3 hospital sites

Site	Phase 1	Phase 2
**GHH**	Control	Realtime audiovisual feedback only

**BHH**	Control	Realtime audiovisual feedback plus post event debriefing

**SH**	Control	Control

### Rationale for study design

The use of the initial control phase at all sites enables within-site comparison of each intervention with standard care, while the inclusion of Solihull as a control site allows the estimation of the effect of the interventions to be adjusted for changes over time due to changes in other aspects of resuscitation care.

The prospective cohort approach has been chosen because of the risk that the significant learning effect from the feedback amongst the cardiac arrest team could contaminate the results if procedures were individually randomised to the two new interventions or the control. This learning effect would similarly limit the applicability of a cross over trial as a prolonged wash-out period between interventions would be required and even this would not guarantee that any learning from the intervention would not be retained by participants.

### Cardiac arrest team

The cardiac arrest team is activated by contacting a central switchboard (2222). The cardiac arrest team at each site consists of: a Resident Medical Officer (Specialist Trainee year 1-3 or equivalent), critical care doctor, Foundation Year 1 doctor, critical care outreach nurse, senior sister on duty for the hospital and hospital porter. The teams are ALS qualified and work to common practices and procedures. The teams are based at a single site and do not rotate between sites.

### The Q-CPR system

Existing Trust defibrillators (MRX, Phillips, UK) will be upgraded with Q-CPR technology (Figure 1). Briefly, a 10 × 5 cm device (containing an acceleratometer and force detector) is placed on the patient's chest during resuscitation and measures chest compression parameters. Real-time audio and visual feedback is provided on chest compression rate, depth, incomplete release and duration of interruptions in chest compression. Ventilation rate is calculated from changes in transthoracic impedance measured through the defibrillator pads. The technical details and validation of this device have been previously published [10]. The CPR-review facility captures and exports these data along with continuous ECG, transthoracic impedance and voice recordings of the resuscitation attempt, thus providing audio and detailed visual data about the resuscitation attempt, without the need for potentially cumbersome video recording equipment.

**Figure 1 F1:**
[figure not shown]
**MRX defibrillator with Q-CPR**.

### Real-time feedback

The Q-CPR system will be used to provide real-time audio and visual feedback. Audio feedback comprises spoken messages that are corrective when the performance of CPR deviates from a defined list of parameters. Examples of voice prompts include: 'Blow in more air'; 'Press down deeper'; 'Switch over faster to compressions'. Visual feedback provides information on the adequacy of chest compression depth, compression and ventilation rates and the duration of interruptions in CPR.

### Post-event debriefing

Post-event debriefing will focus on the importance of the quality of CPR and adherence with this during the arrest, the management of the arrest itself (compliance with guidelines), a review of factors leading up to the cardiac arrest and critique of team management. This will be supplemented by a weekly review and debriefing meeting. This will use the approach developed by the Chicago group [17] of reviewing in detail 3-4 cardiac arrests per week - focusing on quality of CPR, treatment decisions and review of the current literature. The results of these meetings will be feedback to the Trust Resuscitation Committee and Trust Safety Committee (Chaired by [name], Co-applicant and Executive Director for Governance) to report any health system factors that may require addressing.

### Guidelines change in 2010

The International Liaison Committee for Resuscitation and European Resuscitation Council (UK) published new resuscitation guidelines on 18^th ^October 2010. These were incorporated into clinical practice by the trust in December 2010. The Q-CPR feedback devices will be updated to coincide with the adoption of the new guidelines before the implementation phase begins. The control site (Solihull) will allow for estimation of the interventions to be adjusted for changes due to the new guidelines.

### Data Collection

The following data will be exported from the clinical audit database. No patient identifiable information will be transferred from the clinical database to the research team. Date, time and location of arrest; patient demographics (age, sex); details/quality of emergency 2222 call; suspected cause of cardiac arrest; Q-CPR-download containing information on quality of CPR; resuscitation team composition/qualifications/time since last training; post resuscitation care (duration hospital/ITU length of stay); patient outcomes (survival, cerebral performance category at discharge) and interventions performed (airway, defibrillation, drugs).

### Q-CPR interrogation

Objective CPR performance and ECG data will be downloaded from the study defibrillators and analysed using Q-CPR review software (Phillips, UK). Cardiac rhythm at the start of the resuscitation, as well as before and after defibrillation will be extracted from ECG recordings. The defibrillator will be configured to record CPR quality parameters (compression rate, depth, ventilation rate, no-flow fraction (which represents the fraction of time within a given period that a pulseless patient went without chest compressions) [20]. The duration of pre and post-shock pauses will be calculated manually from the ECG and compression depth waveforms. The time to first shock (for patients initially presenting in a shockable rhythm) will be derived from the time of the cardiac arrest call (recorded at the central switchboard) with the time of shock delivery. The Trust defibrillators are synchronised on a monthly basis with the central switchboard time which achieves a co-efficient of variation in times of < 2%.

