### Outcome Measures

The primary outcome for the trial is intial cardiac arrest survival (defined as sustained (> 20 minutes) return of spontaneous circulation). The secondary outcomes are split into two categories; patient focused and process focused outcomes. The patient focused outcomes include: any return of spontaneous circulation; survival to hospital discharge and cerebral performance category of patients at discharge. The process focussed outcomes focus on both quality of CPR and team factors. Quality of CPR outcomes are: quality of 2222 call; chest compression depth; chest compression rate; no-flow time; no-flow time adjusted; duration of pre-shock and post shock pause; ventilation rate; time to first shock (if initial rhythm VF/VT) and appropriate decision to shock. Team factors are; CPR knowledge amongst the cardiac arrest team and confidence/preparedness.

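### The coefficient of variation below 2% does not show that the switchboard and defibrillator clocks agree closely enough for time to first shock; record the offset in seconds and correct for it

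*Protocol article*

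**What the plan says.** The Protocol article, Outcome Measures, includes among the CPR-quality outcomes "time to first shock (if initial rhythm VF/VT) and appropriate decision to shock".

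Q-CPR interrogation explains the measurement. The interval is "derived from the time of the cardiac arrest call (recorded at the central switchboard) with the time of shock delivery". The start is therefore a switchboard time. The source of the shock time is not stated outright, but the same section says "Objective CPR performance and ECG data will be downloaded from the study defibrillators", so the defibrillator clock is the natural reading. On agreement between the clocks it says that the defibrillators are "synchronised on a monthly basis with the central switchboard time which achieves a co-efficient of variation in times of < 2" per cent.

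The section does not say what the 2% is relative to. It gives no offset or drift in seconds, no typical time to first shock and no correction for each event. Monitoring of Data Quality provides for double reading of rhythm and of the pauses around shocks, but not for a check of clock agreement.

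**The concern.** An interval taken across two clocks carries the whole difference between them. That difference is additive: a defibrillator running 20 s fast adds 20 s whether the true interval is one minute or five. A coefficient of variation is a standard deviation divided by a mean, so it needs a mean to be interpretable, and it describes scatter. Clock readings have an arbitrary zero, so their coefficient of variation has no fixed meaning. A shift shared by all devices does not enter the standard deviation at all.

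The figure is therefore offered as reassurance on a question it cannot answer. At stake is the precision of one secondary outcome and, in a particular pattern of offsets, its freedom from bias. Protection against Bias treats data taken directly from the defibrillators as free of bias. That argument does not fully cover this outcome, because one end of the interval comes from another source.

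**Working it through.** **Inputs from the Protocol article**
- Synchronisation is monthly, taken as 30 days (Q-CPR interrogation).
- Coefficient of variation is below 2%, with no mean, standard deviation or unit (same section).
- There are three sites and two phases, with each intervention at one site and Solihull as control throughout (Table 1).
- The analysis model has period and centre effects (Statistical Analysis).

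**Assumed inputs (not in the documents)**
- Time to first shock: 60 to 300 s.
- Drift: 0.1 to 2 s per day, linear, reset monthly.
- True SD of the interval: 120 s.

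**Step 1: the plan's own figure.** It cannot be reproduced, because no mean or SD is given. Converted to seconds as 0.02 × reference mean:
- interval of 60 / 120 / 180 / 300 s: 1.2 / 2.4 / 3.6 / 6.0 s
- time of day, 12 h (43,200 s): 864 s = 14.4 min
- time of day, 24 h (86,400 s): 1,728 s = 28.8 min

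**Step 2: what the figure cannot see.** If every defibrillator is ahead by b, the measured interval is X + b. Its coefficient of variation is SD(X)/(mean(X) + b): the numerator is unchanged and, for positive b, the ratio falls. A small value is therefore compatible with a large shared offset.

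**Step 3: size of the offset.** Month-end offset = 30 × drift. With arrests spread evenly over the month, the mean offset is half of that and the error SD is (month-end offset)/√12. Information kept = 120²/(120² + error SD²).

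| Drift, s/day | Month-end offset, s | Share of 180 s | Mean offset, s | Error SD, s | Information kept |
|---|---|---|---|---|---|
| 0.1 | 3 | 2% | 1.5 | 0.9 | >99.9% |
| 0.5 | 15 | 8% | 7.5 | 4.3 | 99.9% |
| 1 | 30 | 17% | 15 | 8.7 | 99.5% |
| 2 | 60 | 33% | 30 | 17.3 | 98.0% |

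If devices drift in either direction at up to 2 s per day, so that offsets spread evenly from −60 to +60 s, the SD is 120/√12 = 34.6 s and 14,400/(14,400 + 1,200) = 92% is kept.

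For the month-end offset to stay within 2% of a 180 s interval, drift could be at most 3.6/30 = 0.12 s per day. The documents neither support nor exclude that.

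**Step 4: when it becomes bias.** With three sites, two phases, and period and centre effects, the effect at an intervention site (before covariate adjustment) is the change there minus the change at Solihull. Let o be the mean clock offset in a site and phase. The bias is (o at the intervention site in phase 2 − o there in phase 1) − (o at Solihull in phase 2 − o there in phase 1). It is zero if offsets are constant within each site, and zero if they shift equally at all sites. It is non-zero only if the change between phases differs by site. For example, a 30 s mean offset (2 s per day, one direction) confined to one intervention site in one phase would bias the estimate by 30 s, and more patients would not reduce it.

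**The case against.** The strongest case against is that this is a wording gap in a condensed article. The full protocol is an additional file that is not shown, and the basis of the 2% may be given there. Read as variation in the measured interval, 2% is only a few seconds. The outcome is one of about ten CPR-quality measures and is not among those with a stated detectable change in Power and Sample Size. At plausible drift the loss of information is small. All of this stands and limits the weight of the point. It does not rescue the statistic: even on the favourable reading, a measure of scatter says nothing about a shared or systematic offset.

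Stronger readings are tempting, and the documents do not support them:
- **The interval is mostly drift, or zero or negative.** For intervals of 60 / 120 / 180 / 300 s, half the interval is drift on day 30 only at 1 / 2 / 3 / 5 s per day, and the whole interval only at 2 / 4 / 6 / 10 s per day. The documents give neither a drift rate nor a typical interval. Within the assumed range, only the extreme corner (60 s and 2 s per day, at month end) reaches zero.
- **A fifth to a half of the information is lost.** That needs an error SD of 60 s (14,400/18,000 = 80% kept) or 120 s (50% kept). An SD of 60 s requires about 3.5 s per day in both directions or 6.9 s per day in one.
- **Clock error is confounded with the intervention.** Guidelines change in 2010 says the feedback devices will be updated before the implementation phase, but says nothing about resetting clocks. A reset would be one more synchronisation in a monthly routine, and a shift common to all sites is removed by the control site and the period effect.
- **The wrong interval was chosen.** Call-to-shock is a legitimate measure of system response. One arm adds debriefing on arrest and team management, and quality of the emergency call is itself an outcome. Power-on to shock would change what is measured.

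**Conclusion.** The point holds in a limited form. The stated coefficient of variation is undefined and is the wrong kind of statistic. It does not show that the two clocks agree closely enough for an interval of minutes. On assumed drift of 0.1 to 2 s per day the month-end offset is 3 to 60 s. With an assumed true SD of 120 s, at least 98% of the information is kept if drift runs in one direction, and about 92% if it runs in both at up to 2 s per day. Bias in the intervention effect would need offsets that differ by both site and phase, which the documents neither show nor exclude. The conclusion also rests on the shock time being read from the defibrillator, which is implied and not stated.

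The reach is one secondary process outcome in the VF/VT subset. The primary outcome, the sample size and the measures read from the defibrillator alone (compression depth and rate, pauses, ventilation rate) are unaffected. It is a low-cost improvement, worth making because an offset not noted at the time cannot be recovered later.

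**What to change.** 1. State in Q-CPR interrogation that the shock time is read from the defibrillator clock.
2. At each Q-CPR download, record the defibrillator clock against switchboard time, and correct call-to-shock by that difference.
3. Replace the coefficient-of-variation statement with the mean and range of the recorded offsets, in seconds, by site and phase.
4. Keep call-to-shock as the defined outcome. Time from defibrillator power-on to first shock, both read from one clock, may be added as a supportive measure only, since it leaves out the delay before the device arrives.

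The cost is one extra field at a download that already takes place, plus a change of wording. No additional patients are needed.

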### Monitoring of Data Quality

Patient/event data collected by the PDA are checked for fidelity using a detailed periodic re-abstraction process. Initially all data records will be reviewed until an error rate of < 2% is achieved. After this, random sampling of event records will be undertaken by clinical audit staff. This process has been used successfully in multi-centre CPR trials previously [2]. Data requiring manual calculation from the Q-CPR system (rhythm, pre and post shock pauses) will be measured by two researchers and inter-observer agreement calculated and reported. Disagreement will be resolved by re-review and consensus between original 2 researchers.

### Serious Adverse Events (SAEs) and Serious Adverse Device Effects (SADEs)

SAEs and SADEs will be reported to the trial management team if they fulfil the criteria for seriousness, they are potentially related to trial participation, and they are unexpected i.e. the event is not an expected occurrence for patients who have had a cardiac arrest.

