### Eligibility Criteria

Consecutive hospitalised adult patients who sustain a cardiac arrest during their hospital stay will be eligible for inclusion in the study according to the following criteria.

Individual patients will be eligible if:

1. The patient is known or believed to be aged 18 years or over.

2. The patient sustains a cardiac arrest and resuscitation is attempted (defined as loss of a pulse requiring the delivery of chest compressions).

Exclusion criteria will be:

1. If the patient has a Do-not-attempt resuscitation order written and docummented in their medical records

2. The cardiac arrest is not attended by a resuscitation team

3. If the cardiac arrest occurs out-of-hospital

4. Previous participation in this study

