### Power and Sample Size

The sample size estimation is based on a baseline return of spontaneous circulation rate of 44% (from the last 12 month audit at the Trust). To predict a 16% absolute improvement in ROSC rate (as seen in the Edelson et al [17] study which had a similar baseline rate as our Trust) 152 patients will be required in each arm to achieve 80% power at a significance level of 0.05.

Secondary outcomes: Based on the data from the Edelson study and our own preliminary studies (n = 6); the study will have sufficient power (80%) at a significance level of 0.01 to detect the following improvements in CPR quality performance data (all figures are relative changes from baseline): chest compression depth (8%); ventilation rate (12%); no flow fraction (18%); appropriate decision to shock (15%).

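### Serious device effects are reported only if they are not expected after cardiac arrest, so compression injuries that the device may have caused can be screened out

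*Protocol article*

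**What the plan says.** The safety section of the protocol article is a single sentence that covers both kinds of event. It opens "SAEs and SADEs will be reported to the trial management team if they fulfil the criteria for seriousness" and adds two further conditions: "they are potentially related to trial participation, and they are unexpected". It then defines the last of these: "they are unexpected i.e. the event is not an expected occurrence for patients who have had a cardiac arrest".

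Four other sections bear on how that rule works.

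- **Eligibility Criteria:** a cardiac arrest with attempted resuscitation is "defined as loss of a pulse requiring the delivery of chest compressions", so every patient in the trial receives compressions.
- **Real-time feedback:** the device speaks corrective messages when CPR departs from set parameters. One of the three examples given is "Press down deeper".
- **Power and Sample Size:** an 8% relative improvement in compression depth is among the changes that the study is said to be able to detect.
- **Outcome Measures:** the secondary patient-focused outcomes are "any return of spontaneous circulation; survival to hospital discharge and cerebral performance category of patients at discharge". The primary outcome is sustained return of spontaneous circulation. Injury is not among them.

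**The concern.** An expectedness test that refers to the underlying condition is sensible for SAEs. Serious events are very frequent after cardiac arrest, and most reflect the arrest itself. The same test does a different job when applied to device effects. The foreseeable harm of a device that coaches compression depth is more injury, or worse injury, of the type that compressions already cause. That harm resembles the background against which the rule judges expectedness, so an event can be judged serious and potentially related to the device and still not be reported.

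What is at stake is the meaning of the SADE count, not the primary result. If few or no SADEs are reported, the reader cannot tell whether the device did no harm or whether the rule removed the harm it was most likely to do. Patients are enrolled without prospective consent (Consent section), which makes an informative safety route more important.

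**Working it through.** No arithmetic decides this point, and the article states no safety figure to reproduce. The check is to follow one type of event through the rule.

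1. **Structure.** The conditions are joined by "and" in the sense of a cumulative test: report = serious AND potentially related to trial participation AND unexpected. Failing any one means no report. SAEs and SADEs share the test, and the article describes no separate route for SADEs.

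2. **Reference for expectedness.** It is what occurs in patients who have had a cardiac arrest. It is not the known or anticipated effects of the device.

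3. **Background in this population.** By the eligibility definition all patients receive compressions, so injuries of the kind that compressions commonly cause belong to that background. The article does not say this in so many words. It is an inference, but a direct one.

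4. **Device mechanism.** The prompts include one to compress more deeply, and greater depth is an intended effect. A change in compression injury is therefore a plausible consequence of the intervention.

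5. **Event followed through.** Take a serious compression injury in a feedback-phase patient that the clinician thinks the prompts may have contributed to:
   - serious: met
   - potentially related: met
   - unexpected for a cardiac arrest patient: can fail, because the type of injury is common after CPR
   - result: not reported, although relatedness was accepted

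6. **Event of unusual kind or severity.** The same steps with an atypical or exceptionally severe injury can end in a report, because the article sets no severity threshold and lists no expected events. The rule therefore loses the typical injuries, not necessarily all of them.

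7. **Other routes in the article.** Outcome Measures has no injury outcome. Data Collection lists survival, cerebral performance category and interventions performed among the exported items, but no injury item. Harm severe enough to affect survival or cerebral performance would enter those outcomes, but it could not be identified there as injury, and lesser harm would not appear.

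**The case against.** The strongest reply is that the article condenses a full protocol (Additional File 1, cited under Trial Approvals and Conduct) that is not at hand. Lists of expected events, severity rules and a separate SADE pathway are commonly left to such a document. This stands in part: the absence of an injury outcome or data field is not held against the article. But the expectedness definition, and its application to SADEs, is text that the article states.

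A second reply is that the rule governs reporting to the trial management team, not clinical documentation, and that a narrow rule suits a population in which the Consent section expects more than 80% of attempts to be unsuccessful. This stands for SAEs. For SADEs, relatedness is already a condition, so the arrest-based test adds little protection against unrelated reports and removes related ones.

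A third reply is that the device steers towards set parameters, is updated to the adopted guidelines, and has prompts that do not concern depth. That is true, and the article gives no evidence that injury would rise. The point is that the rule could not show it if it did.

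Three stronger readings are tempting but not supported:

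- **That every compression injury is excluded and reports would be close to zero.** With no list of expected events and no severity threshold shown, a severe or atypical injury could still be judged unexpected.
- **That control-phase and Solihull patients can yield no reports because they have no intervention.** The rule refers to trial participation, not to the intervention. Compression depth is an outcome measured against baseline, baseline data are collected at all sites, and depth comes from the chest-placed sensor. Control patients thus appear to be exposed to the sensor, though not to feedback.
- **That a number of missed injuries can be given.** The article contains no injury rates, so any such count would be invented.

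**Conclusion.** The concern holds in a limited form. As written, the rule allows serious injuries of a kind common after CPR to go unreported even when they are judged potentially related to the device. A low SADE count would therefore not be informative about device harm. No magnitude can be given from the documents.

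The conclusion rests on two assumptions: that typical compression injury counts as expected in resuscitated patients, which the article implies but does not state, and that the full protocol does not already provide a separate SADE route. If it does, only the article's wording needs to be brought into line. Neither the primary outcome nor the sample size is affected. The change is worth making because it is cheap and because the trial would otherwise have a weak basis for any statement about the safety of its device.

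**What to change.** In the section on SAEs and SADEs, separate the two kinds of event. For SAEs, keep the three conditions, including expectedness judged against cardiac arrest. For SADEs, remove the arrest-based expectedness condition, so that any serious event judged potentially related to the device or its feedback is reported to the trial management team. Check this against the full protocol and align the two texts if it already has a separate SADE route.

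The cost is a wording change and somewhat more reports to process. Treatment, eligibility and analysis do not change.

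As an option only, serious compression injury already documented in routine records could be tabulated by site and phase. It should be labelled descriptive. Documentation is likely to depend on surviving long enough to be examined, so an intervention that improved return of circulation could raise the documented count with no true increase in injury.
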